**3.Subgroup Analysis**			
≤ 28w vs. > 28w	Gestational age affects adherence	All outcomes	Same as above

*OAC* oropharyngeal administration of colostrum, *FC* fold change, *PCA* principal component analysis, *PLS-DA* partial least squares discriminant analysis, *PCOA* principal co-ordinates analysis, *LDA* linear discriminant analysis

Subgroup analysis will be performed on preterm infants with gestational age ≤ 28 weeks (Table 1).

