In the first 48–72 h the treatment group will receive the treatment measures: two 1 mL sterile syringes each aspirated with 0.1 mL of colostrum, placed at room temperature for 5 min. The colostrum will be maintained at room temperature for OAC use. After removing the tip and cap of the first syringe, the colostrum will be slowly injected along the right oral mucosa for at least 20 s. Then, the right buccal mucosa will be wiped with a sterile cotton swab for at least 10 s. The second syringe will be used in the same way on the left oral mucosa. The procedure will be performed every three hours for five days. The control group will be treated with sterile water following similar operation steps. Colostrum for the control group will be frozen in the NICU breast milk refrigerator for enteral feeding. Vital signs will be monitored throughout the process, including heart rate, respiration, body temperature and pulse oxygen saturation. During treatment, newborns will be regularly monitored and observed. If their clinical symptoms are unstable (heart rate is greater than 200 or less than 100, breathing is greater than 80, or the oxygen saturation is maintained above 85% only when the oxygen concentration increases by 10%) [44], the intervention will be interrupted. Once the clinical situation stabilizes, the treatment will be resumed immediately, and the final intervention dose and adverse reactions recorded.

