### Statistical analysis

Intention to treat (ITT) method will be used for statistical analysis. Baseline maternal and infant demographic and clinical characteristics of OAC group and placebo group will be compared using chi-square or Fisher’s exact test (such as infant sex, mode of delivery and presence or absence of chorioamnionitis) and t-test or Wilcoxon test for continuous variables. After removing low-quality sequences, original data will be analyzed following the steps of 16S rRNA discovery, clustering and identification. The number of operational taxonomic units (OTUs) will be calculated for each sample at a 97% sequence similarity level. A specific taxonomic unit will represent a specific species. Subsequently, a sparse curve will be drawn based on the results of OTUs generated using sample sequencing. Wilcoxon test will be used to analyze the diversity and richness of microbiota within individuals. A t-test or Wilcoxon test will be used to compare alpha diversity (Shannon index, Simpson index, and Chao1 index) between the two groups of infants with and without OAC intervention within four weeks of birth. Repeated measures analysis of variance (ANOVA) (for normally distributed data) or Kruskal Wallis test (for non-normal data) will be used to evaluate the microbial alpha diversity at different time points. The proportion difference of gut microbiota at the phylum and genus levels will be calculated using chi-square or Fisher's exact test. Values with *p* < 0.05 will be considered statistically significant. Beta diversity will be calculated using the Vegan package, and a principal co-ordinates analysis (PCOA) based on Bray–Curtis distances will be plotted. Adonis permutational multivariate analysis of variance of Bray–Curtis distances with 9999 permutations will be used to compare microbial community structure between each of the two groups.

Redundancy analysis (RDA) will be performed using the Vegan package to define the factors that could significantly affect gut microbial composition in each group. We will use Linear discriminant analysis (LDA) of effect size (LEfSe) to determine the most discriminant taxa between the two groups. If the effect of OAC intervention on gut microbiota is less than that of other confounding factors (delivery mode, antibiotic use, feeding type, etc.), we will adjust it with RDA.

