Gut microbiota can regulate the signal pathways regulating intestinal mucosal homeostasis through the production of metabolites. Non-targeted LC–MS will be used to evaluate short chain fatty acids and other organic acids and alcohols. The relative and absolute concentrations of metabolites will be calculated using fold change (FC) value, and the difference in metabolite expression between the two groups will be explored. Principal component analysis or partial least squares discriminant analysis will be used to compare different metabolites among the sample types. A time dynamic curve will be used to further analyze metabolites of interest. The correlation between the relative abundance of dominant bacterial taxa based on 16S rRNA gene sequencing and the intensity of metabolites of interest will be determined using sparse partial least squares regression [45].

Details of all methods of analysis are provided in Table 1.

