### Randomization

A 1:1 block randomization scheme will be adopted. Each group will be stratified by birth gestational age (< 28 weeks, 28 weeks, and 32 weeks). A random serial number will be randomly generated for each layer using SAS (v9.4 SAS Inst. Inc., Cary, NC) before the start of the study. The block length will be 6. Statisticians will prepare sealed, numbered, opaque envelopes for each site and hand them over to the study coordinator, who will ensure that the envelopes are used in a numerical order. After receiving the notice, the study coordinator will open the envelope, take down the group assignment form, copy the form and send it to the statistician. The manuscript will be left in the case file of the preterm infant. To achieve blinding, the study coordinator preparing the syringe (colostrum or placebo) will be different from the nurse conducting the intervention. The subjects, intervention nurses, the principal investigator and the data verifier will be blinded. During the pilot test, non-fixed codes will be used for blinding to represent each allocation scheme to prevent unblinding by inadvertently losing blindness to all trial participants.

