### Missing data

Retention of participants will be ensured during the monitoring period through the support of mothers, lactation encouragement and provision of psychological services. The following events are considered as follow-up losses: the study is not continued due to neonatal death, unstable clinical symptoms and other reasons; the intervention dose does not reach the expected 70%; and parents of preterm infants withdraws from the trial at any time. Eliminated or corrected observations and related reasons will be recorded for future reference.

Most types of missing data in the study will come from random missing. All missing data will be processed with SAS software using the double-robust inverse probability weighting method [53]. Its underlying principle is to estimate the weighted average of the outcome indicators of the complete data sample. Among them, the weight of each individual is the reciprocal of the probability that the outcome index of the individual is not missing, yielding an effect estimation closer to the real value.

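### The subgroup row in Table 1 states a hypothesis about adherence, but its measure and method test neither adherence nor a difference in OAC effect by gestational age

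*Protocol article*

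**What the plan says.** The last row of Table 1 (Subgroup Analysis) has four entries. The contrast is ≤ 28 weeks against > 28 weeks, and the hypothesis is "Gestational age affects adherence". The outcome measure is all outcomes, and the method is the same as for the rows above. The sentence below the table is narrower: "Subgroup analysis will be performed on preterm infants with gestational age ≤ 28 weeks".

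The outcomes that the row takes over (1a to 2f) are Shannon, Simpson and Chao1 indices, short chain fatty acids, phylum and genus proportions, beta diversity, and the correlation of microbiota with metabolites. The methods that it takes over are t or Wilcoxon tests, chi-square tests, fold change, PCA/PLS-DA, PCOA and LDA. For alpha diversity, the Statistical analysis section says: "A t-test or Wilcoxon test will be used to compare alpha diversity (Shannon index, Simpson index, and Chao1 index) between the two groups of infants", the groups being those with and without OAC. The same section ends: "Details of all methods of analysis are provided in Table 1".

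Adherence appears in two other places. The section on milk collection and administration has "the final intervention dose and adverse reactions recorded". The Missing data section counts an infant as a follow-up loss if "the intervention dose does not reach the expected 70" percent.

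**The concern.** A hypothesis, a measure and a method should fit together, and in this row they do not. A test of OAC against sterile water in infants ≤ 28 weeks asks whether OAC changes the outcome in those infants. The answer can be yes or no whatever gestational age does to adherence. Nor does it show that the OAC effect differs by gestational age, because that needs a contrast of effects between the two subgroups.

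At stake is interpretation. A subgroup result could be reported against a hypothesis that the test never addressed, or a significant result in one subgroup beside a non-significant one in the other could be taken as a gestational-age effect. Adherence also matters elsewhere in the plan, because the 70% dose threshold decides who counts as lost. If gestational age does affect adherence, it affects who is lost, and the question deserves a direct answer.

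**Working it through.** **Reading the row.** There are three ways to read it:

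- *Arms compared within a subgroup.* This tests for an OAC effect on microbiota or metabolites in that subgroup. The sentence below Table 1 supports this reading.
- *Infants ≤ 28 weeks compared directly with infants > 28 weeks.* The row's contrast allows this. It tests whether microbiota or metabolites differ by gestational age, which is neither adherence nor a difference in OAC effect.
- *Adherence as the reason for expecting a different OAC effect.* This needs a treatment-by-gestational-age contrast, and none of the listed methods contains one.

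The mismatch therefore stands under every reading and needs no arithmetic.

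**Reproducing the plan's figures.** From the Sample size section: difference 0.2, SD 0.6, two-sided alpha 0.05, power 80%.

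- Normal approximation: n per arm = 2 × (1.960 + 0.842)² × (0.6/0.2)² ≈ 141.3, rounded up to 142. The t-test solution is 142.2, which gives the stated 143.
- Short chain fatty acids (0.025, SD 0.06): the t-test solution is 91.4, which gives the stated 92.

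Both reproduce, and no stated number is wrong.

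**Illustration of separate subgroup tests.** The inputs are 143 evaluable infants per arm, SD 0.6, and a true OAC effect of 0.2 in both subgroups, so there is no effect modification. The share of infants ≤ 28 weeks is not in the document; I assume 20% to 50%.

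- Power in a subgroup with n per arm: Φ(0.2 / (0.6 × √(2/n)) − 1.96).
- Probability that exactly one subgroup is significant: p1(1 − p2) + p2(1 − p1).
- Standard error of the interaction: 0.6 × √(2/n1 + 2/n2). Its power for a 0.2 difference in effect is Φ(0.2/SE − 1.96), and the difference detectable with 80% power is 2.802 × SE.

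| Share ≤ 28 w | n per arm ≤ 28 / > 28 | Power ≤ 28 w | Power > 28 w | Exactly one significant | Interaction power for 0.2 | Detectable at 80% |
|---|---|---|---|---|---|---|
| 20% | 28.6 / 114.4 | 0.242 | 0.713 | 0.610 | 0.203 | 0.497 |
| 30% | 42.9 / 100.1 | 0.339 | 0.655 | 0.550 | 0.252 | 0.434 |
| 40% | 57.2 / 85.8 | 0.430 | 0.588 | 0.512 | 0.281 | 0.406 |
| 50% | 71.5 / 71.5 | 0.513 | 0.513 | 0.500 | 0.291 | 0.398 |

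Check of the first row:

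- Power ≤ 28 weeks: 0.6 × √(2/28.6) = 0.159, 0.2/0.159 = 1.26, and Φ(1.26 − 1.96) = 0.242.
- Exactly one significant: 0.242 × 0.287 + 0.713 × 0.758 = 0.610.
- Interaction: SE = 0.6 × √(2/28.6 + 2/114.4) = 0.177, and Φ(0.2/0.177 − 1.96) ≈ 0.20.

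With equal effects in both subgroups, an interaction test at the 0.05 level would reject about 5% of the time.

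**The case against.** The strongest defence is that this is one short cell in a condensed article. It can be read as the reason for choosing the subgroup: gestational age may affect how much of the intervention an infant receives, so all outcomes are examined by gestational age. Modelling details of subgroups are commonly left to an analysis plan, and the article nowhere says that separate p-values will be read as a difference between subgroups.

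Part of this stands. A missing interaction term alone would be an omission and no finding. But the row does state a hypothesis, a measure and a method, and the text points to Table 1 for the details of all methods. Even on the kindest reading, the stated hypothesis is not tested.

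Two stronger readings are tempting, and the document does not support them:

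- A reader might take the 24-51% rejection rate in infants ≤ 28 weeks as an inflated false-positive rate. It is not. In that scenario OAC truly works, so this is ordinary power; with no OAC effect, the same test would reject at its nominal 5%.
- A reader might expect the adherence comparison to be well powered. The document gives neither a spread nor an expected difference for doses received, so no power can be stated. The 286 infants of the sample size calculation are also the number before the allowance for losses, and infants below the 70% threshold count as losses. A calculation on 286 would leave out the low adherers.

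The 50-61% figure also has a limit. It needs both subgroups to be tested, as the row's contrast suggests. If only infants ≤ 28 weeks are analysed, as the sentence below the table says, the figure does not apply, but then there is no second subgroup from which to infer a difference.

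**Conclusion.** The point holds as a mismatch between hypothesis, measure and method in one row of Table 1. As written, the subgroup analysis answers neither whether gestational age affects adherence nor whether the OAC effect differs by gestational age.

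The numbers only illustrate the second part. They rest on the protocol's own effect and SD, 143 evaluable infants per arm, an equal effect in both subgroups, separate tests of both, and an assumed 20-50% share of infants ≤ 28 weeks. Under these assumptions the two tests disagree about half the time or somewhat more, through limited subgroup power.

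Severity is low. The primary comparisons and the sample size do not depend on this row.

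**What to change.** Decide which question the row is meant to ask, and align its entries and the sentence below the table. Both parts can be kept if both questions matter.

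- **Adherence.** Make the measure the proportion of scheduled doses given. One administration every three hours for five days is 8 × 5 = 40. Compare it between ≤ 28 and > 28 weeks in all randomised infants, including those below the 70% threshold. Adjust for arm and use a method suited to a bounded proportion that may cluster near its upper limit. The dose received is already recorded.
- **Differential OAC effect.** Restate the hypothesis. Fit a treatment-by-gestational-age interaction in all infants for day-7 Shannon index and short chain fatty acids. Report the effect in each subgroup with a confidence interval, and draw no conclusion from separate subgroup p-values.

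While the row is open, check its cut at 28 weeks against the Randomization section: "Each group will be stratified by birth gestational age (< 28 weeks, 28 weeks, and 32 weeks". As printed, the strata do not match ≤ 28 against > 28 weeks.

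The cost is one reworded row and, for the second part, a regression model beyond the planned t or Wilcoxon tests. The interaction has only about 20-29% power for a 0.2 difference in effect, and 80% power needs a difference of about 0.40 to 0.50. It must be labelled exploratory, and a non-significant result must not be read as showing equal effects.

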### Statistical analysis

Intention to treat (ITT) method will be used for statistical analysis. Baseline maternal and infant demographic and clinical characteristics of OAC group and placebo group will be compared using chi-square or Fisher’s exact test (such as infant sex, mode of delivery and presence or absence of chorioamnionitis) and t-test or Wilcoxon test for continuous variables. After removing low-quality sequences, original data will be analyzed following the steps of 16S rRNA discovery, clustering and identification. The number of operational taxonomic units (OTUs) will be calculated for each sample at a 97% sequence similarity level. A specific taxonomic unit will represent a specific species. Subsequently, a sparse curve will be drawn based on the results of OTUs generated using sample sequencing. Wilcoxon test will be used to analyze the diversity and richness of microbiota within individuals. A t-test or Wilcoxon test will be used to compare alpha diversity (Shannon index, Simpson index, and Chao1 index) between the two groups of infants with and without OAC intervention within four weeks of birth. Repeated measures analysis of variance (ANOVA) (for normally distributed data) or Kruskal Wallis test (for non-normal data) will be used to evaluate the microbial alpha diversity at different time points. The proportion difference of gut microbiota at the phylum and genus levels will be calculated using chi-square or Fisher's exact test. Values with *p* < 0.05 will be considered statistically significant. Beta diversity will be calculated using the Vegan package, and a principal co-ordinates analysis (PCOA) based on Bray–Curtis distances will be plotted. Adonis permutational multivariate analysis of variance of Bray–Curtis distances with 9999 permutations will be used to compare microbial community structure between each of the two groups.

Redundancy analysis (RDA) will be performed using the Vegan package to define the factors that could significantly affect gut microbial composition in each group. We will use Linear discriminant analysis (LDA) of effect size (LEfSe) to determine the most discriminant taxa between the two groups. If the effect of OAC intervention on gut microbiota is less than that of other confounding factors (delivery mode, antibiotic use, feeding type, etc.), we will adjust it with RDA.

Gut microbiota can regulate the signal pathways regulating intestinal mucosal homeostasis through the production of metabolites. Non-targeted LC–MS will be used to evaluate short chain fatty acids and other organic acids and alcohols. The relative and absolute concentrations of metabolites will be calculated using fold change (FC) value, and the difference in metabolite expression between the two groups will be explored. Principal component analysis or partial least squares discriminant analysis will be used to compare different metabolites among the sample types. A time dynamic curve will be used to further analyze metabolites of interest. The correlation between the relative abundance of dominant bacterial taxa based on 16S rRNA gene sequencing and the intensity of metabolites of interest will be determined using sparse partial least squares regression [45].

Details of all methods of analysis are provided in Table 1.

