## Outcomes

Primary outcome measures: 1a) a between-group difference in gut microbial alpha diversity will be measured using Shannon diversity index at the 7th day and 1b) a between-group difference in the concentration of fecal metabolites (short chain fatty acids) will be quantitatively measured using non-targeted liquid chromatography-mass spectrometry (LC–MS) at the 7th day.

Secondary outcome measures: 2a) between-group differences in other diversity indicators of gut microbiota, including Simpson index (an indicator of species richness and evenness less affected by rare species than Shannon index) and Chao1 index (estimated total number of species) at the 7th day; 2b) between-group differences in alpha diversity of gut microbiota measured using Shannon index, Simpson index and Chao1 index on the 14th, 21st and 28th days of life; 2c) Between-group differences in the concentration of fecal metabolites quantitatively measured by non-targeted LC–MS at the 14th, 21st and 28th days of life; 2d) proportion of gut microbiota at phylum and genus level; 2e) gut microbial beta diversity explaining between-sample dissimilarity calculated using the Vegan package; and 2f) correlation between the comparative dominant flora and metabolites (Table 1).

**Table 1 Tab1:** Outcomes, measures and methods of analysis

Outcome	Hypothesis	Outcome Measure	Methods of Analysis
**1.Primary** 1a A between-group difference in Shannon diversity index at the 7th day	OAC increases Shannon diversity and metabolites of gut microbiota	Shannon index (continuous)	Individuals: Wilcoxon text; Intergroup: T/Wilcoxon text
1b A between-group difference in fecal metabolites at the 7th day		Short chain fatty acids (continuous)	Individuals: FC, PCA/PLS-DA Intergroup: T/Wilcoxon text
2.** Secondary** 2a Between-group differences in other alpha diversity indexes (Simpson, Chao1) at the 7th day	OAC increases other alpha diversity and beta diversity, and changed the proportion of gut microbiota from birth to day 28. There is a Correlation between dominant microbiota and metabolites	Simpson index, Chao1 index (continuous)	Individuals: Wilcoxon text; Intergroup: T/Wilcoxon text
2b Between-group differences in Shannon index, Simpson index and Chao1 index at the 14th, 21st and 28th days of life		Shannon index, Simpson index, Chao1 index (continuous)	Individuals: Wilcoxon text; Intergroup: T/Wilcoxon text

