### Data collection

Descriptive and clinical data be collected from both groups. Birth status characteristics, such as delivery mode, gestational age, weight and length, Apgar score will be collected in addition to the mothers’ occupation, education level, disease, use of drugs, supplements and antibiotics. During hospitalization, clinical data will be collected on enteral feeding (start time, duration, starting dose, feeding type and total enteral feeding time); parenteral nutrition (start time and duration); antibiotics use in infants (type, start time, duration and dose); NEC, LOS and mortality; and respiratory support.

We hypothesize that OAC would regulate gut microbiota and its metabolites in very preterm infants, resulting in an increase in microbial diversity, with increasing dominance of Lactobacillus/Bifidobacterium predominating and a relative decrease in Proteus species. Stool samples will be collected from selected subjects at the first defecation, as well as on the 7th, 14th, 21st and 28th days and immediately frozen at − 80 °C. Fecal samples refrigerated with dry ice will be transported to the Microbiology Research Institute of Shenzhen People’s hospital. After extracting DNA from frozen fecal samples, 16S rRNA gene will be amplified by polymerase chain reaction (PCR) (v3-v4 hypervariable region) and sequenced using Illumina miseq platform. All data collection procedures will be performed following the local coronavirus disease 2019 (COVID-19) epidemic prevention and control policy.

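### The primary day-7 Shannon test is fixed as unadjusted although randomisation is stratified by gestational age, and the stated strata do not fit eligibility

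*Protocol article*

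**What the plan says.** **Primary test.** Under Outcomes, the first primary endpoint is "a between-group difference in gut microbial alpha diversity will be measured using Shannon diversity index at the 7th day". Table 1 gives its methods as "Individuals: Wilcoxon text; Intergroup: T/Wilcoxon text", and the Statistical analysis section says the same: "A t-test or Wilcoxon test will be used to compare alpha diversity (Shannon index, Simpson index, and Chao1 index) between the two groups". That section closes with "Details of all methods of analysis are provided in Table 1", so the table is presented as complete. No stratified or covariate-adjusted analysis of Shannon appears in either place.

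**Randomisation.** The allocation is 1:1 in blocks of six. "Each group will be stratified by birth gestational age", with three labels: below 28 weeks, 28 weeks and 32 weeks. The statisticians prepare "sealed, numbered, opaque envelopes for each site". Site is not named as a stratification factor.

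**Eligibility and subgroup.** Inclusion requires a gestational age below 32 weeks. For the subgroup, "Subgroup analysis will be performed on preterm infants with gestational age" of 28 weeks or less; Table 1 sets this against more than 28 weeks and repeats the main methods, with no interaction test.

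**First stool.** "Stool samples will be collected from selected subjects at the first defecation" and then at days 7 to 28. The article does not say whether the first stool precedes randomisation or dosing.

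**The concern.** Stratifying the randomisation treats gestational age as prognostic. Stratified allocation removes most of the between-arm variation due to the strata. An unadjusted t-test still counts that variation in its standard error, so if the strata predict the outcome its intervals are wider and its p-values larger than the design warrants. At stake is precision on a primary endpoint, which could be recovered from data already recorded.

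The strata raise a second, textual problem. They define how infants are allocated, and any analysis by stratum needs them. As printed they do not describe the eligible population.

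**Working it through.** **1. Reproduce the planned size.** Inputs from the Sample size section: difference 0.2, SD 0.6, two-sided alpha 0.05, power 80%. The two-sample t-test (noncentral t) needs 142.25, rounded up to 143 per arm, which is the stated figure. Its power at 143 is 80.2%. The sample size therefore belongs to an unadjusted t-test and is correct for it.

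**2. Effect of ignoring the strata.** Let R² be the share of day-7 Shannon variance explained by the randomisation strata. The article does not give it, so a range is shown. With the arms balanced on the strata:

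- true variance of the difference: (1 − R²) × 2 × 0.6² / 143
- variance used by the unadjusted test: 2 × 0.6² / 143
- actual alpha = 2 × [1 − Φ(1.96 / √(1 − R²))]
- unadjusted power = Φ((z − 1.96) / √(1 − R²)), where z = 0.2 / (0.6 × √(2/143)) = 2.819
- adjusted power: t-test with residual SD 0.6 × √(1 − R²)

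Example, R² = 0.10: 1.96 / √0.90 = 2.066, so alpha = 0.039. Unadjusted power: 0.859 / 0.949 = 0.905, Φ = 81.7%. Residual SD = 0.569, giving adjusted power of 84.2%.

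| R² (assumed) | Actual alpha, unadjusted | Power, unadjusted | Power, adjusted |
|---|---|---|---|
| 0 | 0.050 | 80% | 80% |
| 0.05 | 0.044 | 81.1% | 82.2% |
| 0.10 | 0.039 | 81.7% | 84.2% |
| 0.20 | 0.028 | 83.1% | 88.1% |

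The unadjusted column uses the normal approximation and the adjusted column the noncentral t; at R² = 0 the two give 80.5% and 80.2%. The unadjusted standard error is too large by 1 / √(1 − R²): 1.05 at R² = 0.10 and 1.12 at 0.20.

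**3. Simulation check.** 286 infants, blocks of six within two strata (35/65) by three sites (25/33/42), 6,000 replicates; the splits are assumptions.

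| Strata R² | Alpha, unadjusted / adjusted | Power, unadjusted / adjusted |
|---|---|---|
| 0 | 0.046 / 0.046 | 79.8% / 80.0% |
| 0.10 | 0.040 / 0.052 | 82.5% / 84.6% |
| 0.20 | 0.033 / 0.054 | 82.8% / 88.4% |

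Simulation standard errors are about √(0.05 × 0.95 / 6000) = 0.003 for alpha and √(0.83 × 0.17 / 6000) = 0.005 for power. The formulas and the simulation agree in direction and size; the simulated alpha is slightly nearer 0.05 because incomplete blocks leave a little imbalance.

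**4. Does anything else supply the adjustment?** The redundancy analysis in the Statistical analysis section is triggered by the observed results, acts on community composition and does not name gestational age. The inverse probability weighting under Missing data addresses missing outcomes and names no covariates. Neither changes the Shannon test.

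**5. Strata against eligibility and subgroup.**

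| Reading of the strata | Fit with eligibility (< 32 weeks) | Fit with subgroup (≤ 28 / > 28) |
|---|---|---|
| Literal: < 28; 28; 32 | 29 to 31 weeks have no stratum; the 32-week stratum is empty | Fits: ≤ 28 is the first two strata together |
| Repaired: < 28; 28 to < 32 | Fits | The cut divides the upper stratum at 28 weeks |

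Neither reading fits both.

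**The case against.** An unadjusted test after randomisation is valid, the sample size agrees with it, and choosing a linear model is a matter of efficiency. Covariate lists are often left to an analysis plan. The first part stands: there is no bias and no inflated error rate. The second is weak here, because the article names the test and says that Table 1 holds the details of all methods.

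Several stronger readings are tempting but not supported:

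- **Power rises from 80% to 84–90%.** A reader might set adjusted power against the planned 80%. For the strata that is the wrong comparator, because stratified allocation already lifts the unadjusted test to about 82 to 83% at R² of 0.10 to 0.20. At R² = 0.10 the simulated gain is 84.6 − 82.5 = 2.1 points.
- **Site is a stratification factor.** Envelopes per site suggest separate lists, but only gestational age is declared.
- **Infants are without a stratum and the subgroup also splits one.** These defects belong to alternative readings and cannot both hold.
- **The subgroup comparison is invalid because it is not a stratum.** A comparison within a baseline subgroup is still randomised. Only the balance that stratification would give is lost.
- **Any first stool passed before dosing is a safe baseline.** The intervention depends on collecting colostrum, whereas water is always available. If start times differ by arm, a cut at first dose depends on arm. Only a stool passed before randomisation is clearly safe.

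The strata wording may well be a drafting slip for a range from 28 to 32 weeks. It still needs correcting, because it defines the allocation.

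**Conclusion.** The point holds as a should-fix on efficiency and clarity. The primary Shannon test is valid and 143 per arm is right for it. It is conservative to the extent that gestational age predicts day-7 Shannon. At an assumed strata R² of 0.10 to 0.20, alpha is about 0.04 to 0.03 and adjustment adds roughly 2 to 6 points of power; at R² = 0 it adds nothing. These figures assume near balance within strata and a t-test.

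The conflict between strata and eligibility needs no assumption. It is plain in the text, and the subgroup cut cannot be squared with the natural repair.

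**What to change.** 1. Before the interim analysis of the primary endpoint (Quality control section), define the primary analysis as a linear model of day-7 Shannon on arm, gestational-age stratum as randomised, and site. Keep the Wilcoxon test as sensitivity analysis.
2. Add first-stool Shannon only for stools passed before randomisation, with a missing-value indicator for the rest. If few qualify, leave it out; the stratum adjustment does not depend on it.
3. State the strata actually programmed, showing that they cover every eligible infant. The lists were to be generated before the start and the trial is recruiting, so this is a clarification of what was done. If the lists do have a gap, report how infants of 29 to 31 weeks were allocated.
4. Use the same gestational-age cut for the subgroup and test it by an arm-by-stratum interaction.

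The cost is a protocol clarification and a few lines of analysis wording. No new data and no change in sample size are needed.
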